###### Equipment Setup

The only in-person aspect of T0 will be when a member of the research team visits the participant’s residence to set up the VR equipment (Oculus Quest 2) and teaches them how to use and store the device. In teaching participants how to use the VR HMD, participants will practice using the device set to a neutral scene that is not expected to provoke anxiety in people with epilepsy according to phase 1 or existing literature. After using the VR HMD, participants will complete the VRISE questionnaire (Textbox 3) to record their baseline motion sickness tendencies. Note that anyone who scores below 25 on VRISE after using VR with a neutral scene will not be allowed to continue with the study.

At this time, the researcher will review the overall layout of the experiment and arrange a schedule with the participant for the exposure sessions, which will take place daily over one-on-one video calls. Ideally, the video calls (and therefore, exposure sessions) will take place at approximately the same time each day. Indeed, exposures should be performed at similar times each day to limit inconsistent and extraneous reasons for increased baseline anxiety levels.

##### Exposure Session Protocol (T1)

###### Overview

The VR-ET intervention will consist of an exposure session every day for up to 14 days over a one-on-one video call with a researcher. During each exposure session, the participant will be seated in a chair at their home. Exposures will be performed for approximately 5 minutes, which is lower than the recommended 10-minute threshold for mitigating motion sickness [42]. Each day that the participant performs an exposure, they will complete assessments: SUDS 3 times; the Fast Motion Sickness Scale; and, although not a formal assessment, participants will be asked about the frequency in which they used coping mechanisms during the exposure session and in the 10-minute period afterward (Textbox 5).

Assessments at T1.
**Subjective Units of Distress Scale (SUDS)**
The purpose of collecting SUDS scores will be to quantitatively assess:How participants’ anxiety in anticipation of performing the exposure compares to their anxiety immediately after completing the exposureIf their anxiety decreases over time after completing an exposure session (ie, immediately after the exposure vs 10 minutes after the exposure)If their overall anxiety progressively decreases over the course of each exposure levelEach day that they perform an exposure, the participant will record a SUDS score at 3 time points:Before putting on the head-mounted display and beginning the exposure. This measures the anxiety that the participant feels in anticipation of performing the exposure.Immediately after completing the exposure10 minutes after completing the exposure
**Fast Motion Sickness Scale [43]**
The purpose of collecting Fast Motion Sickness Scale scores will be to quantitatively measure motion sickness, specifically the general discomfort and nausea components, that participants may have experienced during the virtual reality exposure session. Participants will complete this assessment shortly after completing the first postexposure SUDS.

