**Virtual Reality Induced Symptoms and Effects (VRISE) assessment [41]**
The VRISE assessment is one of the 4 domains included in the Virtual Reality Neuroscience Questionnaire and evaluates the intensity of motion sickness. The 3 other domains included in the Virtual Reality Neuroscience Questionnaire (user experience, game mechanics, and in-game assistance) are not relevant to our study. A lower score on the VRISE assessment suggests greater motion sickness.Note: Participants who score less than 25 on the VRISE assessment after virtual reality training during T0 will be withdrawn from the study.

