## Discussion

### Principal Findings

Although the primary anxiety treatments for people with epilepsy are cognitive behavioral therapy and pharmacological treatments, minimal research has investigated anxiety treatments specifically for this population [51,52]. Moreover, few studies have investigated the use of ET for treating anxiety in people with epilepsy [24,25]. No studies to our knowledge have delivered ET to people with epilepsy using VR, despite VR-ET’s efficacy in other populations and the benefits that it could offer to people with epilepsy [11].

The main amendments made to the protocol included changes to the phase 3 anxiety assessments, after consultation with a clinical neuropsychologist who specializes in treating people with epilepsy. Indeed, when assessing anxiety in people with epilepsy, it is important to use validated assessments that do not inquire about physical manifestations of anxiety that may be confused with consequences of the neurological disorder. For example, the Beck Anxiety Inventory has been shown to be potentially less accurate in measuring anxiety in people with epilepsy because it contains items that reflect antiseizure medication side effects and symptoms of epilepsy, as opposed to symptoms of anxiety [39]. The Generalized Anxiety Disorder-7 scale was removed because it focuses on generalized anxiety disorder rather than anxiety in general or epilepsy-specific fears. Instead, the EASI was added.

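### Motion sickness is rated only after VR use, and on different scales at T0 and T1, so symptoms already present cannot be separated from VR-induced ones

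*Protocol article*

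**What the plan says.** **T1 (exposure sessions).** The Overview of the Exposure Session Protocol lists what is collected each day: "they will complete assessments: SUDS 3 times; the Fast Motion Sickness Scale", plus a question on coping mechanisms. Textbox 5 fixes the time of the FMS: "Participants will complete this assessment shortly after completing the first postexposure SUDS". Its stated purpose is to "quantitatively measure motion sickness, specifically the general discomfort and nausea components". For SUDS, the same textbox places the first of three ratings "Before putting on the head-mounted display and beginning the exposure". Table 1 shows the FMS at T1 only.

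**T0 (baseline).** The FMS is not given. Under Equipment Setup, participants try the headset with a neutral scene, and then: "After using the VR HMD, participants will complete the VRISE questionnaire (Textbox 3) to record their baseline motion sickness tendencies". A VRISE score below 25 at that point ends participation. Table 1 and the T2 assessments do not repeat VRISE.

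**Role of the two scales.** Principal Findings says that VRISE and the FMS were included to assess motion sickness tendencies and symptoms after the sessions.

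**The concern.** The FMS is there to show whether the headset sessions are tolerated. A single rating after each exposure shows how much discomfort and nausea a participant reports, but not how much of it was there before the headset went on. SUDS has a rating before and ratings after in every session; the FMS has no rating before. The T0 score does not fill the gap, because it comes from another instrument and is itself taken after VR use.

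Feasibility is the primary objective, and the results are meant to shape a larger trial. With five participants and no control group, comparison within the person is the only reference available for tolerability. As planned, a participant who arrives at sessions already uncomfortable cannot be told apart from one made uncomfortable by the headset. The timing is stated in the article, so this is not a detail left to a fuller document, and ratings that were not collected cannot be recovered by analysis.

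**Working it through.** The article gives no figure to reproduce here. The check consists of the assessment schedule, a count of ratings, and what each rating can identify.

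**Schedule side by side**

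| Occasion | Before headset use | After headset use |
|---|---|---|
| T0, neutral scene | no motion-sickness rating | VRISE, once |
| T1, each session | SUDS only | SUDS, FMS, then SUDS at 10 minutes |
| T2 | none | neither VRISE nor FMS |

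**Count.** Inputs: 5 participants (Phase 3 Recruitment); 12 sessions expected, up to 14 (Exposure Session Timeline). All participants are assumed to complete.

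- FMS after exposure: 1 × 12 to 14 = 12 to 14 per participant; × 5 = 60 to 70 in all.
- FMS before exposure: 0.
- SUDS: 3 × 12 to 14 = 36 to 42 per participant, of which 12 to 14 are before exposure.

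A within-session change can be formed for anxiety in every session, and for motion sickness in none.

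**What the ratings identify.** As a simplifying assumption, take the reported score as a sum of parts: *b*, symptoms already present; *v*, the effect of the headset; *a₀*, discomfort from anticipatory anxiety; *a₁*, discomfort from anxiety at the post-exposure rating.

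- Planned post-exposure FMS: *b* + *v* + *a₁*. One observation, three unknowns.
- Difference between two sessions *s* and *t*, as planned: (*b_s* − *b_t*) + (*v_s* − *v_t*) + (*a₁,s* − *a₁,t*). A constant *b* cancels, but so does a constant *v*. Comparing levels therefore does not give the headset effect either.
- With an FMS before the headset goes on (*b* + *a₀*): change = *v* + (*a₁* − *a₀*). The term *b* is removed. If *a₀* exceeds *a₁*, the change understates *v*.
- With an FMS before and after the neutral scene, assuming that this scene provokes no anxiety: change = *v_N*, the headset effect without a feared scene.
- Feared-scene change minus neutral-scene change: (*v* − *v_N*) + (*a₁* − *a₀*). This isolates the anxiety part only if the headset effect is the same in both scenes.

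The added ratings deal with symptoms already present. For anxiety-driven discomfort they give a partial handle only.

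**The case against.** **The aim is limited to the session.** Textbox 5 asks about symptoms "specifically the general discomfort and nausea components, that participants may have experienced during the virtual reality exposure session", so a participant might discount what was there before. That stands as a statement of purpose. It does not solve the problem: nausea that was present beforehand and persists is also experienced during the session, and a single score gives no means of subtracting it.

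**The two scales have different jobs.** VRISE screens at T0 and the FMS describes sessions; the article never proposes subtracting one from the other. This is correct, and no planned analysis fails. The gap is that neither scale has a value without VR.

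**There are mitigations.** Exposures are seated and last about 5 minutes, below the 10-minute threshold the article cites. The neutral-scene screen removes participants who tolerate the headset poorly. SUDS is taken just before the FMS, so the two can be looked at together. Current medication is recorded at T0, and the exit interview asks about experience. These lower the likely level of sickness and help with reading the scores. None supplies a starting value: the medication record is not a symptom rating on the day, and VRISE is not on the FMS scale.

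**The remedy is imperfect.** The extra rating would be taken when anticipatory anxiety is expected, and anxiety that rises during the exposure would still enter the later rating. This stands in full. It is why the raw post-exposure score should be kept beside the change.

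**Conclusion.** The point holds as a measurement gap that is cheap to close. It is neither a contradiction in the protocol nor a threat to its anxiety results. All 60 to 70 planned FMS ratings (if everyone completes) lack a pre-exposure value, and no FMS rating exists for the neutral scene. Discomfort or nausea already present may therefore be read as VR-induced and cannot be separated from it. The size of any resulting error cannot be given, because the article has no data on symptoms before sessions. EASI, PSS and SUDS do not depend on the FMS.

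Four stronger readings are tempting, and the article does not support them.

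- A reader might infer that provoked anxiety and drug side effects will be tallied as VR sickness. The article sets no FMS threshold, event count or decision rule, so only the weaker statement, that the sources cannot be separated, is justified.
- A reader might infer that the two scales run in opposite directions. The article says "A lower score on the VRISE assessment suggests greater motion sickness" but gives no scoring direction for the FMS. The point needs only that the instruments differ.
- A reader might see an inconsistency with the removal of the Beck Anxiety Inventory because "it contains items that reflect antiseizure medication side effects and symptoms of epilepsy, as opposed to symptoms of anxiety". That reasoning concerns an anxiety measure. The article nowhere says that antiseizure drugs cause the symptoms the FMS covers; the Introduction mentions side effects without naming them.
- A reader might cite the usual exclusion of people with epilepsy from VR studies. The article attributes that to concern about triggering seizures, not to motion sickness.

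**What to change.** 1. Give the FMS with the anticipatory SUDS, before the headset goes on, and keep it at its present place after the exposure.
2. At T0, give the FMS before and after the neutral practice scene, next to VRISE.
3. Report for each session both the raw post-exposure FMS and the pre-to-post change, beside that session's SUDS scores and the participant's own neutral-scene change. Keep this descriptive.
4. State in the report that the pre-exposure rating may be raised by anticipatory anxiety, so the change may understate VR sickness, and that discomfort from anxiety arising during the exposure is only partly addressed.

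**Cost.** One more short rating per session (12 to 14) and two at T0: 14 to 16 more per participant, or 70 to 80 over five participants. FMS ratings per participant go from 12 to 14 up to 26 to 30 (2 × 12 to 14, plus 2). All fall on calls or visits already scheduled. The change needs a minor amendment to Table 1 and Textboxes 3 and 5, and adds a small burden for participants.

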**Frequency of coping mechanism use**
After completing the first postexposure SUDS test, participants will be asked how often, if at all, they used the coping mechanisms provided during the exposure (Textbox 2). After completing the second postexposure SUDS test, participants will be asked again about how often, if at all, they used the coping mechanisms since performing the exposure. The purpose of collecting this information is to understand whether differences in the use of coping mechanisms is related to the efficacy of the virtual reality exposure therapy intervention.

The purpose of having a researcher on a video call with the participant during exposure sessions is 3-fold. First, it provides a safety plan in case participants were to have a seizure during the exposure. This was put in place not because it is expected that participants might be triggered by the VR-ET but rather because people with epilepsy are prone to seizures, and therefore, it is important to have a seizure protocol in place. In the background questionnaire, the participant will provide details such as their emergency contact’s information, if they would like the researcher to call their emergency contact or an ambulance if they have a seizure (some people with epilepsy prefer an ambulance not to be called), and if they would prefer for the researcher to keep their video on for safety or to turn it off for privacy. Second, if the participant experiences panic, the researcher will contact an on-call health professional. Third, through discussion with a clinical neuropsychologist, being in someone’s presence (even virtually) while performing an exposure acts as a behavioral commitment from the individual who is receiving the treatment. Therefore, the participant will be less likely to display avoidance behaviors in relation to performing the exposure.

###### Exposure Session Timeline

Each participant will begin with the exposure scene that generates the least amount of anxiety and gradually work their way up to the scene that provokes the most anxiety. Each exposure scene will be performed daily for approximately 4 days, after which the participant will move onto the next level. However, if SUDS scores are >70 and at the discretion of the ETS, the current scene may be repeated until the participant is ready to progress. If a participant’s SUDS score is too high to begin the first level, they will be exposed to a different set and its associated scenes, even if it does not fit with their own anxiety as closely.

As such, the overall schedule may vary for each participant based on their individual progress. The participant is expected to complete the intervention in 12 days but will be allowed up to 14 days if additional days are required to complete a scene. If a participant has a seizure at any point during the 12 to 14 days that they are receiving the intervention, the VR-ET will be discontinued as a precautionary measure. However, data provided up until that point may still be used in analyses and they will participate in T2.

##### Postintervention (T2)

One week after completing the VR-ET intervention, the participant will answer several assessments (Table 1 and Textbox 6), specifically EASI; PSS; Igroup Presence Questionnaire (IPQ) [44]; and the System Usability Scale (SUS) [45]. The proposed diagnostic protocol for epilepsy-specific anxiety disorders [1] will not be repeated at T2 and will instead inform some of the open-ended questions that will be asked in the semistructured exit interview that will take place over telephone or video conferencing (Textbox 6). The interview will be conducted either by an ETS or a member of the research team and will aim to gather additional feedback about the participants’ experience. For example, participants will be asked to provide feedback on their experiences with the various devices, the subjective impact of the therapy, and what may be improved about the program and ET scenarios. Similar to T0, the only in-person aspect of T2 will take place when a member of the research team goes to the participant’s residence to collect the VR equipment.

Outcome measures at T2.Repeat: Epilepsy Anxiety Survey Instrument and Perceived Stress Scale
**Igroup Presence Questionnaire [44]**
The Igroup Presence Questionnaire assesses the subjective experience of being in a virtual environment when one is physically situated in another
**System Usability Scale [45]**
The System Usability Scale assesses usability of the hardware and software
**Semistructured Exit Interview**
To collect feedback (preferences and suggestions for improvement) on the:Virtual reality system usability and trainingVirtual reality exposure scenes(ie, how realistically the videos simulated real-world scenarios that provoke anxiety for the participant)Intervention impact on anxietyTreatment delivery and formatGeneral experience

#### Phase 3 Data Analysis

As both quantitative and qualitative data will be collected in phase 3, a mixed methods approach will be used. Quantitative statistical analyses will be performed using the MiniTAB statistical package [46] and SPSS software (version 27.0; IBM Corp) [47]. To investigate the normal data distributions of the dependent variables, ranges of skewness and kurtosis will be determined. The Kolmogorov-Smirnov and the Shapiro-Wilk tests will also be performed to evaluate statistical significance (mean, 95% CI) and normality of the distributions. In addition, Cronbach *α* will be performed for each self-report questionnaire’s subscales. To explore sociodemographic features, frequencies, means, and standard deviations will be calculated.

To explore the effects of VR-ET, data collected at T0 and T2 will be compared. Clinically significant effects of the intervention will be investigated using the Jacobson-Truax method, based on the measures’ clinical cut-offs (Table 2). Moreover, SUDS scores (before the exposure, immediately after the exposure, and 10 minutes after the exposure) collected every day of T1 will be compared with each other. Participants’ SUDS scores that are recorded immediately after the exposure may be lower than their anticipatory anxiety levels, and if so, this may encourage the participant to do the next exposure. We will also consider our study to be successful if participants’ SUDS scores remain high in the first postexposure SUDS test but decrease at the 10-minute postexposure SUDS test. However, the study may still be deemed successful with unchanging SUDS scores if participants have reduced anxiety and engage in fewer safety-seeking behaviors after completing VR-ET, as based on T2 findings.

Using thematic analysis, qualitative responses to assessments and interviews will be assessed by the research team and then reported as frequencies using the procedure outlined by Braun and Clarke [48]. The constant comparison method will be used to analyze the responses to the open-ended questions asked at T0 and T2 [49].

**Table 2 table2:** Clinically significant scoring for the phase 3 assessments.

		Items	Range	Scores	Citation

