**Coping mechanisms**
Before the baseline interview, participants will be sent a document that provides anxiety coping mechanisms, namely a mindfulness strategy, a self-compassion strategy, and a meditative technique. Participants will be encouraged to practice these coping mechanisms before the interview as they will then review them with the exposure therapy specialist.Before each exposure, the researcher will remind participants that, if they feel too overwhelmed during the exposure, they should remove the virtual reality head-mounted display even if they have not completed the full exposure and use the coping mechanisms that they prepared with the exposure therapy specialist. (If the participant stops the exposure early and uses a coping mechanism, the researcher will make a note of this. Postsession Subjective Units of Distress Scale (SUDS) scores will be recorded regardless.)If the participant scores >70 on any of the SUDS tests after completing the exposure, whether they ended the exposure early or not, they will be instructed by the research member on the video call to use the coping mechanisms. (The remaining SUDS scores will still be recorded.)

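### A SUDS fall 10 minutes after exposure is one ground for study success whether or not the exposure was completed

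*Protocol article*

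**What the plan says.** Three parts of the protocol article bear on this.

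- **Phase 3 Data Analysis.** The SUDS scores "collected every day of T1 will be compared with each other", and the study would be regarded as "successful if participants’ SUDS scores remain high in the first postexposure SUDS test but decrease at the 10-minute postexposure SUDS test". This is not the only route: the same section compares T0 with T2 and allows success on T2 findings even if SUDS does not move.
- **Textbox 2 (Coping mechanisms).** Participants who feel too overwhelmed are told that "they should remove the virtual reality head-mounted display even if they have not completed the full exposure and use the coping mechanisms". For these sessions, "Postsession Subjective Units of Distress Scale (SUDS) scores will be recorded regardless". The researcher's record is described as follows: "If the participant stops the exposure early and uses a coping mechanism, the researcher will make a note of this". A separate rule covers scores above 70 on any of the "SUDS tests after completing the exposure, whether they ended the exposure early or not"; in that case "they will be instructed by the research member on the video call to use the coping mechanisms".
- **Textbox 5 (Frequency of coping mechanism use).** Coping use is asked about after each of the two postexposure SUDS scores, "to understand whether differences in the use of coping mechanisms is related to the efficacy of the virtual reality exposure therapy intervention".

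**The concern.** The success pattern uses two numbers only, the score just after exposure and the score 10 minutes later. A participant who stays in the scene for the planned time and then settles produces the same pattern as one who leaves because it is too much and then settles. These are different results for an exposure treatment. The Background section says that short-term relief from safety behaviours such as avoidance maintains or increases anxiety. Phase 3 Exclusions says, of benzodiazepine use, that avoidance removes the value of an exposure.

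What is at stake is how one success criterion is read, and one feasibility result. The Limitations section makes implementation of the intervention part of the primary goal. How many planned exposures were tolerated to the end bears directly on that goal, and a pooled SUDS reading does not show it.

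**Working it through.** There is no planned figure to reproduce, because the criterion has no threshold, test or sample size behind it. The check sets the texts side by side.

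**1. What the criterion needs.** Call the immediate postexposure score S1 and the 10-minute score S2. The pattern is S1 high and S2 < S1. Completion of the exposure is not an input.

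**2. Which sessions supply S1 and S2.** The comparison takes scores from every T1 day, and Textbox 2 keeps the scores after an early stop. No exclusion or separate display is stated.

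**3. Whether the timing wording implies completion.** Textbox 5 times both later scores from completion of the exposure, which might look like a condition. Textbox 2 rules that out, since it uses the same phrase for sessions stopped early: "SUDS tests after completing the exposure, whether they ended the exposure early or not".

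**4. One session of each kind.**

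| | Early-ended session | Completed session |
|---|---|---|
| Reason it ended | Participant overwhelmed | Planned time of about 5 minutes reached |
| S1 | Plausibly high, since overwhelm caused the stop | May be high |
| Between S1 and S2 | Scene left early, coping used | Coping instructed if SUDS > 70 |
| S2 | Plausibly lower | May be lower |
| Meets the pattern if S2 < S1 and S1 high | Yes | Yes |

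The criterion cannot tell the two columns apart. The entries marked plausible are inference; the article gives no data on them.

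**5. What would allow separation.** The early-stop note and the coping questions would largely do it, but the success sentence uses neither.

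**6. Scale.** Planned counts come from Phase 3 Recruitment (5 participants), Phase 2 Protocol (3 scenes per set) and Exposure Session Timeline (about 4 days per scene, 12 to 14 days in all).

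- Sessions per participant: 3 × 4 = 12.
- All sessions: 5 × 12 = 60, or 5 × 14 = 70 if everyone uses 14 days.
- Sessions per level: 5 × 4 = 20.
- One early-ended session is 1/4 = 25% of that participant's sessions at the level, 1/20 = 5% of the level, and 1/60 = 1.7% (1/70 = 1.4%) of all sessions.

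These are shares of planned sessions. They are not estimates of bias and do not show that any conclusion would change.

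**The case against.** The strongest reply is that handling of incomplete sessions is ordinary analysis-plan content, that this is a condensed article, and that the two sections do not contradict each other. That holds for the details of display. It does not dispose of the point, because the article itself states the success criterion and itself sends early-ended sessions into the data behind it.

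A second reply is that the departure from standard exposure therapy is deliberate. The Baseline Interview section explains why coping is allowed in people with epilepsy, and the 5-minute duration is tied to motion sickness rather than to a minimum dose. This is correct. The safety rule is sound and should stay; only the reading of the scores is in question.

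Some stronger readings are tempting, and the text does not support them:

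- *Each early-ended session counts towards success.* The criterion speaks of participants' scores as a pattern and has no per-session tally or threshold. One such session does not make the study a success.
- *Early stops go unrecorded.* The note is worded for stopping early together with coping, but the instruction pairs the two and a researcher is on every call. Only a stop without coping falls outside the wording, which is a narrow gap.
- *Coping is ignored.* It is asked about twice per session and is to be related to efficacy.
- *Early-ended sessions should be dropped.* That would select on tolerance and remove the most distressed sessions from a five-person study. Keeping them is a legitimate choice.

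The pilot also disclaims any assessment of clinical efficacy and discloses that it is uncontrolled and unblinded, which limits the weight of any SUDS finding.

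**Conclusion.** The point holds in a limited form. As written, one ground for calling the study successful can be met by relief after leaving the scene, because the criterion disregards completion and the early-ended sessions stay in the data. This runs against the protocol's own account of avoidance. It affects this criterion only; the T0 to T2 comparison and the T2 findings stand apart from it.

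Its size cannot be determined. The article gives no early-stop rate and none is assumed here. The conclusion rests on the wording of the success sentence and of Textbox 2, and on the inference that a participant who stops because of overwhelm would often score high at first and lower after leaving. It is a worthwhile, low-cost improvement and does not invalidate the pilot.

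**What to change.** Keep the headset-removal rule and keep all sessions in the SUDS comparison. Then:

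1. In Textbox 2, have the researcher note every early stop, with or without coping. Define a completed exposure as one in which the headset was not removed early.
2. In Phase 3 Data Analysis, add wording such as: *SUDS scores will be shown for all sessions, and separately for completed and early-ended sessions, with coping use alongside. Success on the postexposure SUDS pattern will be claimed only if the pattern is also seen in completed sessions. The number of completed exposures per level will be reported as a feasibility result.*

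The cost is one mark in each of 60 to 70 planned sessions, made by the researcher already on the call, plus the added wording. Safety procedures, schedule and sample size do not change.

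The downside is that completed sessions are fewer and selected on tolerance. A fall within them still cannot be put down to habituation alone, because coping is instructed there too when SUDS exceeds 70. The all-session results and coping use therefore have to be shown beside them.
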